### Participant safety and withdrawal

The potential risk level reviewed by institutional review board and principal investigator is minimal. For prevention and management in adverse events, participants can call researchers at any time if they have any question or problems. If there are an intolerable muscle pain or injury, they will visit a hospital and will be examined their condition by principal investigator.

All participants are able to discontinue voluntarily the study at any time and they can be withdrawn in case of the significant disease non-related to study, and not following instruction of doctor in charge.

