## Methods/design

### Study design

This protocol will be a prospective multi-centered single-blinded two-armed RCT. The study design meets SPIRIT guidelines [13] and the SPIRIT Checklist are attached as Additional file 1. All eligible patients will be informed about this study and invited to participate by the outpatient doctor at the Physical Medicine and Rehabilitation clinic in Republic of Korea. All patients submit informed consent if they agree to participate in the study and principal investigator obtained the informed consent. After randomly divided into two groups with a 1:1 allocation, participants will be assessed in baseline. The intervention group will receive at least 3 months of hospital-based physical therapy in conjunction with home-based telerehabilitation. The control group will receive at least 3 months of hospital-based physical therapy in conjunction with a home-based exercise brochure provided by the hospital. The adhesive capsulitis stage will be evaluated at each follow-up by a physician, and exercises according to the stage will be prescribed. Outcomes will be assessed at the baseline and 1-month, 2-month, 3-month, 4.5-month, and 6-month follow-ups. Deviation of 7–15 days from each evaluation point will be allowed. Outcome measures will be performed by the same assessors, who will be blinded to the group allocation. The flow diagram of the study protocol is shown in Figs. 1 and 2.

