**Fig. 3 Fig3:**
[figure not shown]
UINCARE Home+ (left) and screen during exercise with real-time feedback (right) (A: guide video, B: holding time, exercise set and number)

The telerehabilitation protocol using the UINCARE Home+ is shown in Fig. 4. First, the physician will diagnose the patient’s stage of adhesive capsulitis and prescribe a corresponding exercise program. The UINCARE company device manager creates the user account and then, independent researchers set up the prescribed exercise program on the administrator page. The UINCARE Home+ will be delivered by the company, installed at the patient’s home, and the patient will be trained on how to use it. During the intervention period, independent researchers will monitor performance, accuracy, and check individual exercise schedules through the administrator page. Every month, the researcher will enquire of the related problem and encourage the patient to exercise at least once a day.

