### Brochure (usual care)

This group will be offered a brochure in accordance with the patient’s diagnosed adhesive capsulitis stage. They will be asked to record the number of exercises in their exercise log book. During the intervention period, participants were asked to submit the exercise log book every month.

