### Secondary outcomes

The secondary objectives of this protocol are to determine the additive effect of interactive AR-based telerehabilitation in conjunction with hospital-based physical therapy on 1) pain intensity; 2) activities of daily living; 3) quality of life; and 4) shoulder disability over time. Therefore, the secondary outcomes will be active ROM, pain measured with the numeric rating scale, shoulder pain and disability index, 36-Item Short Form Survey, European Quality of Life Five Dimensions Five Level Scale, and Canadian Occupational Performance Measure. Along with the RCT, a satisfaction questionnaire (Additional file 3) and safety assessment will be conducted for both the system and equipment.

As secondary outcomes, active range of motion (AROM), pain and disability of the affected shoulder joint, quality of life, and activities of daily living (ADL) will be considered at all follow-up assessments. The satisfaction questionnaire for interactive AR-based rehabilitation will be evaluated only in the intervention group after 12 weeks.

Supine measurements of PROM and AROM of the affected shoulder will be obtained with the participants lying in a supine position. Shoulder forward flexion, abduction, and external and internal rotation with a 90° shoulder abduction will be measured with an electronic goniometer in units of 1°. All ROMs of each participant will be assessed as described by Kelly et al. [14].

The pain intensity at resting and activity will be evaluated by a 11-point Numeric Rating Scale (NRS) [16] for the past week, with 0 and 10 representing “no pain” and “the worst possible pain”, respectively Participants will be asked for an average perceived pain intensity in ADL.

Shoulder pain and disability for the past week will be assessed using the Shoulder Pain and Disability Index (SPADI), consisting of two subscales with a total of 13 items (five items for pain and eight for disability) [17]. Patients will report a level of difficulty performing ADL due to pain and limit of motion. The final score will range from 0 to 130 with a percentage score of 0 indicating less shoulder disability and 100 indicating more shoulder dysfunction.

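### Exercise-related flares and injuries have no stated like-for-like enquiry in the two arms, and the assessment labelled safety concerns the system and equipment

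*Protocol article*

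**What the plan says.** All references are to the protocol article.

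- **Secondary outcomes** places the safety work beside the satisfaction questionnaire: "a satisfaction questionnaire (Additional file 3) and safety assessment will be conducted for both the system and equipment". Here the word for two things joins system and equipment, not the two arms.
- **Participant safety and withdrawal** gives the reporting route, "participants can call researchers at any time if they have any question or problems", and the response to the named harm, "If there are an intolerable muscle pain or injury, they will visit a hospital and will be examined their condition by principal investigator".
- **Telerehabilitation** adds a contact for the AR arm: "Every month, the researcher will enquire of the related problem and encourage the patient to exercise at least once a day".
- **Brochure (usual care)** describes a different monthly contact, a log book submission: "They will be asked to record the number of exercises in their exercise log book".
- **Study design** gives both arms a physician contact: "The adhesive capsulitis stage will be evaluated at each follow-up by a physician, and exercises according to the stage will be prescribed".
- **Secondary outcomes** also gives both arms a pain score: "The pain intensity at resting and activity will be evaluated by a 11-point Numeric Rating Scale (NRS) [16] for the past week". The Shoulder Pain and Disability Index (SPADI) likewise refers to the past week. Pain and disability are assessed at every follow-up, and Statistical analysis compares secondary outcomes by group over time.

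**The concern.** Both arms follow the same home programme of 30–40 minutes, to be done daily, with strength work added from stage 2. The Discussion expects AR to raise the quantity of exercise done. If it does, AR participants load a painful shoulder more often, so exercise-related pain or injury is the harm on which the arms could plausibly differ. A check of the system and equipment does not address it.

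The remaining routes for transient or injury-type harm are calls, which depend on the participant, and a monthly enquiry described for one arm. Either the harm is under-counted in both arms, or it is solicited in one arm and volunteered in the other. The trial is meant to support digital therapeutics, so a by-arm safety statement is likely to be read closely. As described, it could reflect how participants were asked as much as what happened to them.

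**Working it through.** **Plan figures.** The article gives no harm rate and no safety sample size, so there is no safety figure to reproduce. The efficacy sample size does reproduce. For flexion, with two-sided alpha 0.05/4 = 0.0125 and 80% power:

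n = 2 × (2.498 + 0.842)² × (18.64/15)² ≈ 34.4, rounded up to 35 per group; 35/0.75 = 46.7, rounded up to 47.

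Neither number bears on this point. What matters is the enrolment of 100 at 1:1, which is 50 per arm.

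**Step 1. Stated routes, side by side.**

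| Route | AR arm | Brochure arm | Reaches flares and injuries? |
|---|---|---|---|
| Safety assessment | System and equipment | No telerehabilitation system | Not stated |
| Participant call | Yes | Yes | Only if the participant calls |
| Monthly researcher enquiry | Yes | Not described | Perhaps; may mean device problems only |
| Monthly log book | Not described | Exercise counts | No |
| Physician staging at follow-up | Yes | Yes | No harm question stated |
| Pain scale and SPADI, past week | Yes | Yes | Pain in the past week; no record of muscle injury |

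No row gives the same stated question about exercise harm in both arms.

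**Step 2. Time covered by the pain scores.** Intervention period: 12 × 7 = 84 days. Past-week windows at weeks 4, 8 and 12: 3 × 7 = 21 days. 21/84 = 25%, leaving 63 days outside the recall window. Those days are not unobserved, since participants have hospital therapy and, in the AR arm, the monthly enquiry. They are outside any scored pain measure.

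**Step 3. Under-counting (assumed rates).** Suppose 20% of AR and 10% of brochure participants have a flare: 50 × 0.20 = 10 and 50 × 0.10 = 5. If 1 in 5 calls: 10 × 0.2 = 2 and 5 × 0.2 = 1. The ratio is kept, but the counts are too small to describe.

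**Step 4. Unequal enquiry (assumed capture).** Suppose true rates are equal, capture is 90% with monthly enquiry, and capture c relies on calls. Apparent AR/brochure ratio = 0.90/c:

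- c = 30%: 3.0
- c = 50%: 1.8
- c = 70%: 1.29

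Under this reading the bias runs against AR. If the enquiry concerns the device only, Step 3 applies to both arms instead.

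**Step 5. Would a formal test help?** Power is for a two-sided 5% test of two proportions, n = 50 per arm, complete capture:

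power = Φ{[Δ − 1.96 × √(2p̄(1 − p̄)/n)] / √[(p₁(1 − p₁) + p₂(1 − p₂))/n]}

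- 10% v 20%: (0.10 − 1.96 × 0.0714)/0.0707 = −0.565, power about 29%
- 5% v 15%: (0.10 − 1.96 × 0.0600)/0.0592 = −0.297, power about 38%
- 10% v 30%: (0.20 − 1.96 × 0.0800)/0.0775 = 0.558, power about 71%

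The gain from better ascertainment is therefore a fair description by arm, not a significance test.

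**The case against.** The strongest reply is that the trial already observes both arms repeatedly. Blinded assessors score pain at rest and on activity, and SPADI, at every follow-up, and the plan compares these by group over time. A physician stages every participant at each follow-up, and both arms attend hospital therapy. The call route is open for any question or problem. Adverse event forms and tabulations are commonly left to a full protocol, Table 1 is not shown, and the study was rated minimal risk.

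Much of this stands, and it rules out several stronger readings:

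- *That exercise harm surfaces only through calls.* The monthly enquiry in the AR arm and the staging contacts in both arms contradict this.
- *That the trial cannot compare exercise harm.* A lasting difference in shoulder pain would show in the planned secondary analyses.
- *That only intolerable events are recorded.* That word governs when a participant is examined, not what may be reported.
- *That no adverse event record exists.* A condensed article with a missing table cannot establish this.
- *That the safety assessment is certainly AR-only.* This is the natural reading, but equipment is not defined, and all participants receive a bar, band and dumbbells.

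The reply does not remove the mismatch in the text. The pain scores are efficacy measures of average recent pain: a group mean can improve while a few participants flare, and muscle injury is not recorded in them. The staging contact has no stated harm question. A fuller adverse event form might close the gap, but the stated target of the safety assessment, the stated reporting route and the one-arm enquiry would still need to be reconciled with it.

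**Conclusion.** The point holds in a limited form. On the text shown, transient flares and muscle injuries have no stated like-for-like ascertainment in the two arms. Sustained shoulder pain does have a planned comparison.

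The size cannot be fixed from the article. The 25% coverage is arithmetic on nominal visit weeks and the past-week recall. The fall from 10 and 5 events to 2 and 1 rests on assumed flare and calling rates, and the spurious ratio of 1.29 to 3.0 on assumed capture. Which of the two applies depends on whether the monthly enquiry covers exercise problems or only the device, and the article does not say. The same remedy serves both cases. A reader might infer that a real difference in harm would be detected once ascertainment is mended. At 50 per arm that is unlikely for modest differences, so the matter is the fairness of descriptive reporting. It is a worthwhile, inexpensive improvement and does not threaten the primary result.

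**What to change.** 1. At each existing follow-up (weeks 4, 8, 12, 18 and 24), ask both arms the same fixed question about new or worsened shoulder or muscle pain, or injury, since the last visit. Someone already present who is not the blinded assessor should ask it, so that answers do not reveal allocation to the assessor.
2. Record answers of any severity and report them descriptively by randomised arm, without a formal test.
3. Keep the system and equipment check as a separate AR-only item, and state what equipment means.
4. Reconcile Telerehabilitation, Brochure (usual care), Secondary outcomes, and Participant safety and withdrawal, saying whether the monthly enquiry covers exercise problems and whether both arms receive it.

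A count of participants whose motion in any direction is worse than baseline is not a useful substitute. Motion is read to 1°, and the Background describes stage I as a time of increasing pain and stiffness, so measurement noise and natural history would fill such a table.

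The cost is one question at visits that already take place, with more minor events to record and describe. No visit is added and no treatment rule changes.

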## Abstract

**Background:**

As the primary treatment for adhesive capsulitis, intensive and accurate home exercise is as important as physical therapy in hospitals. Augmented reality (AR)-based telerehabilitation has been implemented recently in various musculoskeletal conditions to increase patient compliance and enable patients to exercise with the correct posture. The objective of this study is to present a protocol for investigating the additive effect of interactive AR-based telerehabilitation in comparison with the usual care for patients with adhesive capsulitis.

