## Background

Adhesive capsulitis, also known as “frozen shoulder,” is a common shoulder disease that clinically presents with pain, stiffness, and dysfunction and is pathologically characterized by inflammation and contracture of the glenohumeral capsule [1]. Although there are differences in the literature, adhesive capsulitis has a high prevalence rate of 2–5% in the general population, with the highest prevalence observed among women between 40 and 60 years of age [2]. Adhesive capsulitis consists of the first “freezing (painful)” stage with increased pain and stiffness for several months, a second “frozen (stiff)” stage resulting in loss of range of motion (ROM) of the shoulder, and a third “thawing (recovery)” stage, in which pain and ROM recover [3].

Adhesive capsulitis is generally described as a self-limiting disorder that without supervised treatment, often recovers within 2–3 years [4]; however, its natural history is not fully known, and recent studies have shown that it may result in long-term disability [1, 4–7]. One systematic review showed that appropriate interventions were essential in reducing long-term disabilities [8]. Rehabilitation including joint mobilization and therapeutic exercise is one of the most important interventions required for adhesive capsulitis [9]. Home exercise programs are as essential as physical therapy in hospital because of cost effectiveness and limited medical resources. Tanaka et al. [10] showed that better compliance with a home exercise program resulted in more improvement in adhesive capsulitis. However, home exercise programs are not easily quantified, and it takes time for doctors to explain and modify postures for each patient. Moreover, the accuracy and frequency of home-based rehabilitation may depend on the patient’s statement, rather than on objective and analyzed data. A key success factor of home-based programs is to increase adherence to the program, for instance through telerehabilitation.

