### Interventions

Regardless of group allocation, both groups will receive physical therapy at the hospital once or twice at least for 3 months. Hospital-based physical therapy will be performed for 1 h in combination with joint mobilization and modality (heat and electrical stimulation by physical therapists with more than 10 years of treatment experience). The therapist will be blinded to the assigned intervention group of the participant.

All patients will be instructed to exercise at home at least once a day with precautions for each exercise stage, exercise posture, method, and frequency. Depending on group allocation, there will only be a difference in the way home exercise is performed, with no difference in the program itself or the type/duration of the exercise. All patients will receive an assistant bar, a yellow elastic band and 0.5-kg dumbbells required to perform the exercises. Exercise will consist of 3 stages according to the adhesive capsulitis stage (i.e., stage I is freezing, stage II is frozen, or stage III is thawing). Every month during the intervention period, the exercise stage will change according to the stage of the adhesive capsulitis. All exercises will consist of a warm-up, scapular stabilization, shoulder ROM exercises, and shoulder stretching. The details of the exercise differ by step (Additional file 2), and strength training is added from the frozen stage (stage 2). The stepwise exercise will be the same for both groups and consist of 11–16 types of exercise, ten times per set, with a total exercise time of 30–40 min. Exercise contents of each stage were determined based on the literature [14, 15].

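### The withdrawal rule allows randomised participants to be removed from the study for not following instructions, so poor adherers can be lost at different rates by arm, with a bias of unknown direction

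*Protocol article*

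**What the plan says.** The Participant safety and withdrawal section first gives participants the right to leave: "All participants are able to discontinue voluntarily the study at any time". The same sentence then gives grounds on which they may be taken out: "they can be withdrawn in case of the significant disease non-related to study, and not following instruction of doctor in charge". Because the sentence is about leaving the study, its natural reading is removal from the trial and not only from the exercise. The article does not say that a withdrawn participant still attends the 12-week visit.

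The Interventions section makes home exercise an instruction in both arms: "All patients will be instructed to exercise at home at least once a day". It adds that between the arms "there will only be a difference in the way home exercise is performed".

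The article names adherence as a route to benefit. The abstract describes AR telerehabilitation as used "to increase patient compliance and enable patients to exercise with the correct posture". The Background states: "A key success factor of home-based programs is to increase adherence to the program, for instance through telerehabilitation". It also cites a study in which better compliance went with more improvement. The Discussion expects gains in both the amount and the quality of exercise, and describes compliance with brochures as poor.

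Adherence is captured differently in the two arms. For AR, the Telerehabilitation section says that "independent researchers will monitor performance, accuracy, and check individual exercise schedules through the administrator page". For the control arm, the Brochure section says: "They will be asked to record the number of exercises in their exercise log book". The log is handed in monthly.

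**The concern.** In this trial the instruction is a large part of the treatment, so a participant who does not exercise is an obvious candidate for the withdrawal clause. On the article's own premises, non-adherence predicts less improvement and is likely to differ between arms. Withdrawal for it would then be a selection made after randomisation, on something the treatment is meant to change. The participants lost would be those whose results show how well each mode of home exercise holds up in practice.

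Uneven visibility adds to this. Device records and a self-completed log need not reveal the same behaviour equally well, and the clause sets no threshold that would make its use uniform. At stake is the primary outcome, the 12-week change in passive ROM. If that measurement is not taken, defining an analysis set later cannot restore it.

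**Working it through.** **The plan's own figures.** From Sample size calculation: flexion SD 18.64, difference 15, significance level 0.05/4 = 0.0125 per motion, power 80%, dropout 25%. The article does not state sidedness; two-sided reproduces its figure.

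- n per group = 2 × (2.498 + 0.842)² × (18.64/15)² = 34.4, rounded up to 35. The other three motions need 28, 29 and 31, so flexion sets the size.
- 35/0.75 = 46.7, rounded up to 47.

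Both stated figures reproduce. The point does not rest on a sample-size error.

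**Bias formula.** In one arm, let p be the share withdrawn for non-adherence and g the number of degrees by which they improve less than those retained. The full-arm mean is (1 − p) × retained mean + p × withdrawn mean, so the retained mean exceeds the full-arm mean by p × g. The rule covers both arms, so the net bias in the AR-minus-brochure difference is

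bias = p(AR) × g(AR) − p(brochure) × g(brochure).

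**Assumptions (not in the documents).** g is the same in both arms and equals 5, 10 or 15 degrees. Withdrawal for non-adherence is 10% in one arm and 40% in the other, which averages to the planned 25% dropout. Withdrawn participants have no 12-week measurement, and there is no other loss. The true flexion difference is 15 degrees.

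| g (degrees) | AR 10%, brochure 40%: bias | 15 is seen as | 25% in both: bias | AR 40%, brochure 10%: bias | 15 is seen as |
|---|---|---|---|---|---|
| 5 | −1.5 | 13.5 | 0 | +1.5 | 16.5 |
| 10 | −3.0 | 12.0 | 0 | +3.0 | 18.0 |
| 15 | −4.5 | 10.5 | 0 | +4.5 | 19.5 |

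A milder split of 15% AR and 35% brochure gives −1.0, −2.0 and −3.0.

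**Effect on power where the brochure arm loses more.** Of 47 per arm, 47 × 0.90 = 42.3 and 47 × 0.60 = 28.2 remain. The standard error is 18.64 × √(1/42.3 + 1/28.2) = 4.53. Power is Φ(difference/4.53 − 2.498), which gives 68.5%, 56.0% and 42.8% for observed differences of 13.5, 12.0 and 10.5. With 25% lost in each arm (35.25 remaining) and no bias, it is 81.1%. With all 47 per arm measured and a difference of 15, the standard error is 18.64 × √(2/47) = 3.85 and power is 92.0%.

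**Where the AR arm loses more.** The shift favours AR. At its largest, 4.5/4.53 is about one standard error, and it would appear even if the true difference were zero.

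**The case against.** The strongest defence is that the clause permits withdrawal and does not require it. It sits under safety and withdrawal beside unrelated disease, sets no adherence threshold and does not mention exercise frequency. The Telerehabilitation section has independent researchers, not the doctor in charge, watch the device data. The response it describes is a monthly enquiry and encouragement, and nothing links device records or log books to withdrawal. All of this stands. The clause may seldom be used for missed exercise, but nothing in the article prevents that use.

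Four stronger readings are tempting, and the documents do not support them.

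- A reader might infer that the AR arm is inflated because non-adherence is easier to see there. The Discussion expects poor compliance with brochures, which could bring more control withdrawals and a bias the other way. Control non-adherence is not hidden either, since a missing or thin monthly log is visible.
- A reader might compute a bias of 1 to 5 degrees towards AR by taking 10% to 25% withdrawn and a shortfall of 10 to 20 degrees in that arm alone (0.10 × 10 = 1; 0.25 × 20 = 5). That sets the other arm's term to zero, although the rule covers all participants.
- A reader might say that the rule uses up the 25% dropout allowance. The article does not say what the allowance covers, and it may already include such withdrawals.
- A reader might call adherence the mechanism of the trial. The abstract and Discussion also name correct posture, accuracy and real-time feedback.

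The full protocol or analysis plan may define an as-randomised analysis set, and its absence from an article is no fault. Such a set would still not recover measurements never taken.

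**Conclusion.** The concern holds as a risk created by a stated rule. Use of the clause for non-adherence can remove participants selectively after randomisation, at different rates by arm, and lose their primary outcome. On the assumptions above, the net effect on the flexion difference lies between about −4.5 and +4.5 degrees, up to 30% of the planned 15 (4.5/15). It is zero when rates and shortfalls match. The withdrawal rates and the shortfall are assumed, so the range illustrates what is possible and is no estimate. The documents establish neither the sign nor how often the rule will be used. It should be fixed, because a bias of unknown sign cannot be corrected afterwards, but the documents do not show that the comparison is already compromised.

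**What to change.** In Participant safety and withdrawal, separate two events: not following or stopping the assigned exercise, and leaving the study. Record the first as non-adherence, on the same definition in both arms. Continue the scheduled outcome assessments, at least the 12-week passive ROM, unless the participant withdraws consent. State that all participants are analysed in the group to which they were randomised. Decisions about care stay with the physician and are not affected.

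The change is a sentence or two. Recruitment began in March 2020, so it would go through the route for protocol modifications described under Ethics and dissemination. The cost is that some follow-up visits continue that would otherwise have stopped.
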